**Non-intervention sites**

Tuberculosis patients in the non-intervention district will follow the existing facility based tuberculosis case finding and treatment. They will receive supplies and programme managers will carry out supervision according to the existing supervision system.

**Reporting**

District programme managers will report tuberculosis control activities according to the existing reporting system of the region as it carried out on quarterly bases. Reports include cases detected, treated, sputum follow up, drug, supervision laboratory supplies, and request for next quarter. In addition, they will submit research formats to the investigator. They will keep copies of their office.

**2.2. Study variables**

The variables included are socio-demographic, knowledge and attitude towards tuberculosis and the patients, and factors contributing to the willingness to supervise treatment. Community health workers will ask for any antituberculosis drug side effect.

**2.3. Data collection techniques and tools**

Health workers will register all the required information about tuberculosis patients as per the national recommendation and the study. At the end, health workers will hand over all records related to the study to the investigator. They will also report their activities to the health institutions, district, zone and regional level. Data collectors will collect data from the reports and formats prepared for community-based tuberculosis care.

**2.4. Sample size calculation**

The treatment success rate of Sidama zone is 70 %. With the intervention, we assume effect size of 21 % so that to increase the treatment success to 85%, WHO target.

n = [(z1 + z2)*2*P]/

n = the sample size from each group z1 =level of significance of 95 %( 1.96)

z2 =power of the study of 90 %( 1.28) p1 =proportion of treatment success in control group (70%)

p2 =proportion of treatment success in intervention group (85%)

P= the average proportion of treatment success in the control and intervention groups (77.5%)

n = = = 163

IF = 1 + (m-1)*ICC

IF - inflation factor or design effect m - cluster size /15 TB patients

[Based on tuberculosis prevalence of 533 per 100,000, taking case detection rate of 47% as reported by WHO 2005, we expect 15 tuberculosis cases per village of 6000 population.]

ICC - intracluster correlation coefficient assuming typical ICC of 0.04

IF = 1 + (15 - 1) * 0.04 = 1.56 Effective sample size = IF * calculated size = 1.56 * 163 = 255

To calculate number of clusters per group

Total tuberculosis patients divided by cluster size 255 /15 = 17 clusters per group

k - Coefficient of variation = standard deviation of proportions/mean of proportions p1 = 70% p2= 85% P = 77.5% SD =0.106 k =0.12

c = 2 + /

c = 2 + / = 14 clusters

The case detection of all forms of tuberculosis is 47 % of the annual incidence of 356 cases per 105 populations. Assuming that the case detection of all forms of tuberculosis will increase to 70%, we expect case detection of 250 cases per 105 populations. Therefore, to detect 30 cases per cluster we need about 12,000 people. A Kebele /villages have a population of about 6000, in densely populated areas as in Sidama. So a cluster will have two kebeles.) With this case detection, the study will take one year for case detection and additional 6- 8 months to record treatment outcome.

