**1.3 Tuberculosis control programme in Ethiopia**

In Ethiopia, about 60 - 80 % of health problems are because of communicable diseases and malnutrition. Tuberculosis is among the leading causes of death and sickness in the country.[6] A well- organized tuberculosis control programme started in 1992 and the geographic coverage is 71%.[3]

Ethiopia ranks 7th among high tuberculosis burden countries in the world. Ninety five percent of health institutions give DOTS service for population. Unfortunately, 40% of population do not have access to health service. The annual incidence and prevalence of all forms of tuberculosis is 356 and 533 per 105 populations respectively. The case notification rate for all forms tuberculosis is 166 per 105 populations. [4] The annual incidence of smear positive tuberculosis is 155 cases 105 populations. The case notification of smear positive tuberculosis cases is 56 105 populations. The case detection rate of all forms and smear positive cases is 47 % and 36 % respectively. The proportion of patients who are cured and completed treatment (treatment success rate) is about 76 %. [4]

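### Study Two overstates expected cases per cluster: the 15 applies an incidence-based detection rate to prevalence, and the 30 assumes improved detection in control clusters too

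*Protocol*

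**What the plan says.** Two case counts drive the design in Study Two, section 2.4.

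- **Cluster size 15.** The note reads "Based on tuberculosis prevalence of 533 per 100,000, taking case detection rate of 47% as reported by WHO 2005, we expect 15 tuberculosis cases" for a village of 6,000. This m = 15 gives the design effect of 1.56, the 255 patients per group and the 17 clusters per group. Study Three, section 2.4, uses the same m and design effect.
- **Cluster size 30.** The closing paragraph starts from a different base: "The case detection of all forms of tuberculosis is 47 % of the annual incidence of 356 cases per 105 populations". It continues: "Assuming that the case detection of all forms of tuberculosis will increase to 70%, we expect case detection of 250 cases per 105 populations". From this it concludes "Therefore, to detect 30 cases per cluster we need about 12,000 people" and "So a cluster will have two kebeles". One year of case detection is said to follow. Nothing is split by arm.

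Two other places bear on these counts. Section 1.3 gives the rates: "The annual incidence and prevalence of all forms of tuberculosis is 356 and 533 per 105 populations respectively" and "The case notification rate for all forms tuberculosis is 166 per 105 populations". The Non-intervention sites paragraph of Study Two says: "Tuberculosis patients in the non-intervention district will follow the existing facility based tuberculosis case finding and treatment". Section 6.2, Study I, likewise keeps non-intervention clusters on self-reporting.

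**The concern.** A detection rate has meaning only against its own denominator. The protocol's 47% is notified cases over incident cases in a year. Multiplied by prevalence, it gives a count that matches nothing the programme would register in a year.

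The second count has a different fault. Monthly community mobilisation and sputum collection are what could raise detection to 70%, and only intervention clusters receive them. A single figure of 30 per cluster therefore credits the control arm with a benefit that the design withholds from it.

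At stake are the cluster size in the design effect, the number of clusters, the population per cluster and the one-year accrual period.

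**Working it through.** **Inputs from the protocol.** Incidence 356, prevalence 533 and notification 166 per 100,000 (section 1.3). Detection 47% and 70%, kebele of 6,000, cluster of 12,000, ICC 0.04, success 70% against 85%, mean 77.5%, z values 1.96 and 1.28, k = 0.12, and 17 or 14 clusters (Study Two, section 2.4). I take 14, like 17, as a number per arm.

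**1. The protocol's figures reproduce.**
- 533/100,000 × 0.47 × 6,000 = 15.03 (stated 15)
- 356/100,000 × 0.70 × 12,000 = 29.9 (stated 30)
- (1.96 + 1.28)² × 2 × 0.775 × 0.225 / 0.15² = 162.7 (stated 163)
- 1 + 14 × 0.04 = 1.56; 1.56 × 163 = 254.3 (stated 255); 255/15 = 17

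**2. Which base the 47% belongs to.** 166/356 = 46.6%, while 166/533 = 31.1%. It belongs to incidence.

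**3. Yield on that base, per year.**
- Kebele: 356/100,000 × 0.47 × 6,000 = 10.0. Directly from notifications: 166/100,000 × 6,000 = 9.96.
- Two-kebele control cluster: 356/100,000 × 0.47 × 12,000 = 20.1 (from notifications, 19.9).
- Two-kebele intervention cluster: 29.9, if 70% is reached.
- Sensitivity for control: detection of 60% would give 42.72 × 0.60 = 25.6. Only 70% gives 30.
- Reaching 30 control cases at 47%: 30/(0.00356 × 0.47) = 17,930 people for one year, or 30/20.1 × 12 ≈ 18 months in 12,000 people.

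**4. Power by the ICC method.** Effective size per arm is e = C × m / (1 + (m − 1) × 0.04). Power = Φ(0.15/√[0.775 × 0.225 × (1/e₁ + 1/e₂)] − 1.96).

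| Clusters per arm | Cases, control/intervention | e, control/intervention | Power |
|---|---|---|---|
| 17, one kebele | 15/15 (as planned) | 163.5/163.5 | 90% |
| 17, one kebele | 10/10 | 125/125 | 81% |
| 17, one kebele | 10/15 | 125/163.5 | 86% |
| 17, two kebeles | 20/30 | 193.2/236.1 | 96% |
| 14, two kebeles | 20/30 | 159.1/194.4 | 92% |

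Control patients are 17 × 10 = 170 with single kebeles, against 255 planned. With two kebeles they are 17 × 20 = 340 or 14 × 20 = 280. With m = 10 in both arms, the design effect is 1.36, so 1.36 × 163 = 222 patients and 222/10 = 22.2, that is 23 clusters per arm.

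**5. Power by the k method.** The formula for c is broken in the text at hand. I assume the standard pair-matched form: c = 2 + (1.96 + 1.28)² × [p₁(1 − p₁)/m₁ + p₂(1 − p₂)/m₂ + k²(p₁² + p₂²)]/(p₁ − p₂)².
- With 30/30 the bracket is 0.0070 + 0.00425 + 0.01746 = 0.02871 and c = 15.4. The stated 14 is therefore not exactly reproduced.
- With 20/30 the bracket is 0.0105 + 0.00425 + 0.01746 = 0.03221 and c = 17.0.
- Power with 14 clusters = Φ(0.15 × √(12/bracket) − 1.96): 87% at 30/30 and 82.5% at 20/30.
- With 17 clusters at 20/30: 89.9%.

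**The case against.** The strongest reply is that the section ends with two-kebele clusters. A control cluster of 20 then exceeds the m = 15 in the design effect, total control patients exceed 255, and power at ICC 0.04 is above 90% with either cluster count. This stands. A reader might infer from the wrong inputs that the stated 90% power is lost outright, or that the control arm will hold 170 patients. The protocol does not support that as a general statement: both results need single-kebele clusters.

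The k-based result is the one two-kebele case clearly below 90%, and it is weak evidence. It rests on an assumed formula. It already gives 87% with the planned 30/30, so only about 4 points come from the case counts. Its k derives from an SD of 0.106, which is the SD of the two arm proportions 0.70 and 0.85 and not variation between clusters.

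The figure of 15 per kebele can also be reached another way: 356/100,000 × 0.70 × 6,000 = 14.95. But that is the intervention arm at 70%, not the derivation given, and it does not help the control arm.

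Finally, 47% is a national figure, and the protocol gives no all-forms detection rate for Sidama. The control yield of 20 is therefore an assumption. It is nevertheless the figure the protocol itself uses for present detection, and nothing in the protocol would raise control detection to 70%.

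**Conclusion.** The input errors are certain, because the section contradicts its own definition of the 47% and the protocol's description of the control arm. The stated 15 per kebele is about 50% above the 10 that the protocol's rates give. The 30 per cluster is about 50% above the 20 expected in a control cluster, if national detection holds in Sidama. For intervention clusters the 30 follows from the assumed 70%.

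The consequence is conditional:
- single-kebele clusters, 17 per arm: 81% to 86% power instead of 90%;
- two-kebele clusters at ICC 0.04: 96% (17) or 92% (14), so no shortfall against 90%;
- two-kebele clusters at k = 0.12 with 14 clusters: 87% falls to about 82%, on an assumed formula.

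The one-year accrual to 30 cases does not hold for control clusters of 12,000. About 18 months plus the stated 6 to 8 months for outcomes would also run past the September 2006 to March 2008 window in the summary table of studies.

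Excluding patients on re-treatment lowers yields further. The protocol gives no share for them, so I have not sized this.

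**What to change.** In Study Two, section 2.4:

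1. Replace the 15-case note with incidence × 47%: 10 per kebele a year, 20 per two-kebele control cluster. State that 47% is a national rate assumed for Sidama, or substitute a zonal rate.
2. Use 70% for the intervention arm only.
3. State one cluster definition and one number of clusters.
4. Recompute the design effect and number of clusters with unequal cluster sizes (20 and 30 if two kebeles), and carry the revised m into Study Three.
5. Make any allowance for excluded re-treatment patients an explicit assumption.
6. Restate the power and the accrual period.

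The cost is a recalculation, and the stated figures may become slightly less favourable. Larger control clusters or longer accrual are needed only if the restated power falls short under the definition chosen.

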**2.4. Sample size calculation**

Community based tuberculosis care reduced 30% of patient cost in health facility to 13 % in community-based tuberculosis treatment in a study conducted in Tanzania.[34] Based on this

n = [(z1 + z2)*2*P]/

n = the sample size from each district z1 =level of significance of 95 %( 1.96)

z2 =power of the study of 90 %( 1.28) p1 = patient cost in facility based tuberculosis treatment (30%)

p2 = patient cost in community-based tuberculosis treatment (13%)

P= the average proportion of treatment success in the control and intervention groups (21.5%)

n = = = 123

IF = 1 + (m-1)*ICC

IF - inflation factor or design effect m - number of cluster size 15 assuming equal cost per cluster

ICC - intracluster correlation coefficient assuming typical ICC of 0.04

IF = 1 + (m - 1)*ICC = 1 + (15 - 1) * 0.04 = 1.56

Effective sample size = IF * calculated size = 1.56* 123 = 192

In addition, the cost related to tuberculosis treatment supervisors, community health agents, tuberculosis programme coordinators in the district and health institution will be included.

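### Study Two's design effect of 1.56 and its 255 patients per group are computed for 15-case clusters, but the section then adopts 30-case clusters, which need 2.16 and 353 per group

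*Protocol*

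**What the plan says.** Study Two, section 2.4 starts from treatment success of 70% in control and 85% in intervention clusters, with 1.96 and 1.28 as the normal deviates for two-sided 5% significance and 90% power. It obtains 163 patients per group before clustering.

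It then takes a cluster of 15 patients (one village of 6,000 people) and an ICC of 0.04: "IF = 1 + (15 - 1) * 0.04 = 1.56". From this follow the inflated total, "Effective sample size = IF * calculated size = 1.56 * 163 = 255", and 255/15 = 17 clusters per group.

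A second route, through a coefficient of variation, prints 14 clusters. The section closes with a different cluster: "to detect 30 cases per cluster we need about 12,000 people", and "So a cluster will have two kebeles". Neither the design effect nor the 255 is revisited, and the section does not choose between 17 and 14.

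On enrolment, the intervention-sites text in Study Two, section 2.1 includes every diagnosed patient in the selected clusters, subject to listed exclusions. Section 2.4 plans one year of case detection.

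**The concern.** A design effect has to be calculated for the unit that is randomised. The only inflated patient total in Study Two belongs to a one-village cluster, while the section ends by adopting a cluster twice that size. At a fixed ICC, larger clusters carry less information per patient, so a total that suits clusters of 15 is too small for clusters of 30.

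The section also leaves two cluster sizes (15 and 30) and two cluster counts (17 and 14) standing side by side. A reader could take the planned size as 14 × 15 = 210, 17 × 15 = 255, 14 × 30 = 420 or 17 × 30 = 510 per group. Anyone who relies on 255 as the number that secures 90% power would be relying on the wrong figure for the adopted cluster.

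**Working it through.** Inputs, all from Study Two, section 2.4: p1 = 0.70, p2 = 0.85, average P = 0.775, deviates 1.96 and 1.28, ICC = 0.04, cluster size m = 15 or 30.

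**The plan's own figures**
- Before clustering: n = (1.96 + 1.28)² × 2 × 0.775 × 0.225 / 0.15² = 162.7, so 163. Reproduced.
- Design effect at m = 15: 1 + 14 × 0.04 = 1.56. Reproduced.
- Inflated size: 163 × 1.56 = 254.3, so 255; 255/15 = 17 clusters. Reproduced.
- Power at 255 with m = 15: effective n = 255/1.56 = 163.5, power 90.1%. The pairing of 255 with 90% is correct for one-village clusters.

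**The same formula for the adopted cluster**
- Design effect at m = 30: 1 + 29 × 0.04 = 2.16.
- Inflated size: 163 × 2.16 = 352.1, so 353 per group.
- Clusters: 353/30 = 11.8, so 12 per group.

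**Power with 30-case clusters**, as Φ(0.15/SE − 1.96), where SE = √(2 × 0.775 × 0.225 × 2.16 / N) and N is patients per group:
- 14 clusters, N = 420: SE = 0.0424, power 94.3% (95.0% with unpooled variance). A paired t-test with 13 degrees of freedom gives about 90%.
- 17 clusters, N = 510: SE = 0.0384, power 97.4% (97.8% unpooled).
- N = 255: SE = 0.0544, power 78.8% (80.1% unpooled). This means 255/30 = 8.5 clusters per group, a count the protocol does not state.

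**Sensitivity to yield.** The 30 cases rest on detection rising to 70%: about 250 per 100,000 × 12,000 = 30. If detection stayed at 47% of the incidence of 356 per 100,000 (an assumption), two kebeles would yield 0.47 × 356/100,000 × 12,000 ≈ 20 cases. The design effect is then 1 + 19 × 0.04 = 1.76. Fourteen clusters give 280 patients and about 89% power; twelve give 240 and about 84%.

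**The case against.** The strongest reply is that 255 is not a recruitment cap. It belongs with 17 clusters of 15, where it is right. Enrolment is set by the number of clusters and the year of case detection, with all diagnosed patients included. Both printed cluster counts exceed the 12 that clusters of 30 require. The 14 also comes from a separate formula whose terms are lost in the available text, so the cluster size it used cannot be seen.

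This stands as far as the trial's power is concerned. A reader might infer that the trial would run at about 79% power. The documents do not support that: it requires recruitment to stop at 255 in 8.5 two-kebele clusters per group, and the protocol says neither. The reply does not rescue the printed figures. The design effect, the 255 and the 17 are stated results, they describe a cluster other than the one adopted, and the combination that gives adequate power (14 or 17 clusters of 30 per group) is nowhere written down.

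A reader might also extend the point to Study Three, which uses "m - number of cluster size 15 assuming equal cost per cluster" to reach 192. That is not shown either. Spread over 14 or 17 clusters, 192 is about 14 or 11 patients per cluster, which fits an m of 15, and Study Three does not say that all 30 cases per cluster are interviewed.

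**Conclusion.** The point holds as an error in a stated sample size. For the adopted two-kebele cluster of 30 cases, the protocol's own formula gives a design effect of 2.16 rather than 1.56, and a minimum of 353 rather than 255 patients per group, a difference of 98. The printed 255 does not carry 90% power for that cluster.

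No power shortfall is shown for 14 or 17 fully enrolled clusters of 30 per group: about 94% to 98% by the normal approximation, and about 90% for 14 clusters by paired t-test.

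The conclusion takes the protocol's ICC of 0.04 and its 30 cases per cluster as given. It reads the 14 as a count per group; the figure stands under the heading for clusters per group but is not itself labelled so.

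**What to change.** In Study Two, section 2.4:
- Recompute the design effect with the adopted cluster: m = 30, factor 2.16, minimum 353 patients per group.
- Delete 255, and 255/15 = 17, as the target.
- State one cluster size, one cluster count per group and the resulting total. The count should not fall below the printed 14, which gives 14 × 30 = 420 per group and still about 89% power if clusters yield only 20 cases. The 12 clusters implied by 353 are a minimum at 30 cases each and should not replace the larger printed counts.
- Say that all eligible patients in each cluster are enrolled for the full year, so that no patient total is read as a stopping point.

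The cost is a rewording. The stated minimum per group becomes larger, but no enrolment is needed beyond the year already planned.

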**STUDY THREE - TO FIND OUT THE COST PER TUBERCULOSIS PATIENT TREATED SUCCEFULLY**

**1. Objective**

- To find out the costs per tuberculosis patient treated successfully

**2. Methods**

**2.1. Study design**

This is a randomized controlled community trial to find out the costs per tuberculosis patient treated successfully in the intervention and non-intervention districts. Cost related to tuberculosis control programme in the study sites will be determined according to the actual expenses and time cost. Programme coordinators, health workers, community health agents, tuberculosis treatment supervisors, tuberculosis patients and relatives accompanying them to health facilities in the study sites will be included in the study.

The cost analysis will follow societal perspective to analyse the cost per patient. The data collectors will obtain financial reports from districts and health institutions finance sections to collect expenditures for tuberculosis control programme, health workers and community health agents’ time and costs associated to tuberculosis prevention and control activities. In addition, they will collect cost of the patient and the relative who accompanied them during their visit to health institutions.

The investigator will use cost per tuberculosis patient successfully treated as an outcome measure. Future cost and productivity gains will not be included in the study. Standard cost estimation of all expenses and time of the patient, treatment supervisor and health workers will be done. Data collectors will use a structured pre-tested questionnaire for data collection.

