**2. Methods**

**2.1. Study design**

This is a randomized controlled community trial to estimate the tuberculosis treatment outcome through community based tuberculosis care. The investigator will select clusters from study districts. Based on the population, health service coverage and mainly on tuberculosis treatment outcome the investigator will match the clusters. He will match clusters and randomly assign them into intervention and non-intervention groups.

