**2.3. Data collection techniques and tools**

Trained data collectors will administer a pre-tested structured questionnaire. Study variables include socio-demographic variables of tuberculosis patients, financial expenses and time. When the tuberculosis patient is less than 18 years, the data collectors will interview the parents or the guardians accompanying them to health institution. The data collectors will review financial reports of health institutions and the district.

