**COMMUNITY BASED TUBERCULOSIS CARE – DISTRICT FORM**

**Questionnaire no.________ Name of interviewer __________ Date___________**

**Resources for tuberculosis control**

1. Health manpower for tuberculosis control

Profession____________________ monthly salary________ __________

2. Motor bike________________ number ___________

3. Budget allocated for tuberculosis control programme _________________

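### Study III records district programme costs with no cluster or arm identifier and calls the arms districts, although the randomised unit is a two-kebele cluster within districts

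*Protocol*

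**What the plan says.** **Unit of randomisation.** Study Two, 2.1 Study design: "The investigator will select clusters from study districts", and "He will match clusters and randomly assign them into intervention and non-intervention groups". Study Two, 2.4 Sample size calculation sets the cluster size at about 12,000 people: "So a cluster will have two kebeles". The same section arrives at 17 clusters per group by one method and 14 by another.

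**How the arms are described.** Study Three, 2.1 Study design sets out to find the "costs per tuberculosis patient treated successfully in the intervention and non-intervention districts". Study Three, 2.4 defines n as the sample size per district. Study Two, Non-intervention sites says: "Tuberculosis patients in the non-intervention district will follow the existing facility based tuberculosis case finding and treatment".

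**Where programme cost comes from.** Study Three, 2.1: "The data collectors will obtain financial reports from districts and health institutions finance sections to collect expenditures for tuberculosis control programme". Study Three, 2.3 repeats it: "The data collectors will review financial reports of health institutions and the district". The District form in the annex asks for staff and salaries, motor bikes, "Budget allocated for tuberculosis control programme", the number of supervisory visits, hours and kilometres per supervision, and total fuel expenditure. Remaining costs are left to the finance report. The form has no field for cluster, kebele or arm.

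**What the other forms carry.** The TB patient, treatment supervisor (TTS) and community health worker (CHW) forms each have cluster and kebele fields. The laboratory technician and TB OPD forms name the health facility and record hours per activity together with monthly income.

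**The concern.** Cost per patient treated successfully, compared between arms, is the only outcome stated for Study III. Community care adds programme-side work. Section 6.6 allows supervision schedules specific to the intervention, and Study Two (Intervention sites) adds a chain of supervision over treatment supervisors and health extension workers, while control sites keep the existing system. Part of that extra cost falls on district coordinators, their travel and their fuel.

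These items are recorded as district figures. If the arms were districts, a district figure would belong to one arm. With clusters randomised inside districts, one figure can cover intervention clusters, control clusters and kebeles outside the study. The cost of the added supervision could then not be read off the data for the arm that caused it. An analysis plan can state how to divide a joint cost, but it cannot recover which cluster a visit served if nobody wrote it down.

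**Working it through.** **1. The plan's own Study III figure.** With p1 = 0.30, p2 = 0.13 and P = 0.215 (Study Three, 2.4):

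n = (1.96 + 1.28)² × 2 × 0.215 × 0.785 / (0.17)² = 122.6, so 123.

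Design effect 1 + 14 × 0.04 = 1.56, and 1.56 × 123 = 191.9, so 192.

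Both stated figures reproduce, and this point does not dispute them. The calculation labels n as per district but inflates it for clusters of 15 patients, so Study Three's own sample size treats the cluster as the unit.

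**2. Size of the trial against the size of a district.** Section 6.1 gives about 2.8 million people in 10 districts and 2 city administrations.

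- Average district: 2,800,000/12 = 233,333 to 2,800,000/10 = 280,000 people.
- Trial with 14 clusters per group: 28 × 12,000 = 336,000 people.
- Trial with 17 clusters per group: 34 × 12,000 = 408,000 people.
- In district equivalents: 336,000/280,000 = 1.20 to 408,000/233,333 = 1.75.

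**3. Chance that a district holds only one arm.** The number of study districts D is not given, so it is varied as an assumption. Clusters are taken as spread evenly, m = 2c/D per district with c clusters per group, and each cluster's matched partner is taken to lie in another district. The chance that a given district falls wholly in one arm is then about 2 × 0.5^m. If any pair lies within the district, the chance is zero.

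| D | c = 14 | c = 17 |
| --- | --- | --- |
| 2 | 0.01% | 0.002% |
| 3 | 0.3% | 0.08% |
| 5 | 4% | 2% |
| 10 | 29% | 19% |

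Under these assumptions most districts hold both arms, and nearly all do when D is small. An uneven spread could leave some districts with a single cluster and hence one arm.

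**4. What is lost in a mixed district.** Let S be the recorded district cost and q the share caused by the intervention arm, with equal patient numbers. Only S is observed. Using the planned success proportions of 85% and 70% (Study Two, 2.4), the intervention-to-control ratio of cost per success for this component alone is (q/0.85) / ((1 − q)/0.70):

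- q = 0.4: 0.55
- q = 0.5: 0.82
- q = 0.6: 1.24
- q = 0.7: 1.92

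The values of q are illustrative. They show that the direction of the comparison for this component depends on a quantity the form does not capture. They are not estimates of the bias in the total cost.

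**5. Which cost items are affected.**

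| Source | Identifier | Assignable to an arm? |
| --- | --- | --- |
| Patient, TTS and CHW forms | cluster and kebele | yes |
| Laboratory and TB OPD forms | facility, hours per activity | yes, as unit costs times volume per arm |
| District form | none below district | not in a mixed district |
| Remaining costs from finance reports | district or institution | not where the unit serves both arms |

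**The case against.** Much can be said on the other side, and most of it limits the reach of the point.

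- **Much of the community-side cost is identified.** The CHW form records education, sputum transport, drug collection and supervision hours and days by cluster. The TTS and patient forms also carry cluster. A reader might infer that Study III's costs as a whole cannot be assigned to an arm. The forms do not support that.
- **The facility forms are not totals.** Hours per activity and monthly income give a unit cost, which needs no arm field. Volumes can come from forms that record cluster: treatment and follow-up travel on the patient form, and follow-up smears on the treatment outcome questionnaire. The protocol does not spell out this multiplication, but the data would allow it.
- **The district form gives partial clues.** It counts health facilities and community health workers supervised per supervision, which partly separates community from routine supervision. It does not link a visit's hours, kilometres or fuel to a cluster.
- **A total loss of the difference is not shown.** A reader might reason that an intervention-only cost X per patient, split by patient numbers over equal arms, shows X/2 in each arm, so that the whole difference vanishes. That follows only from a split by patient numbers, and the protocol states no split.
- **Mixing at facility level is not shown.** Dividing the zone's population by its 47 treating facilities (1 + 20 + 26) gives about 60,000 people, or five cluster-sized areas each. That counts the whole zone. Only 28 to 34 clusters are in the trial. Spread over the zone, that is 28/47 to 34/47, about 0.6 to 0.7 study clusters per facility, and many facilities could serve one arm only.
- **Apportioning joint overheads is normal in costing.** The allocation key and its sensitivity analysis can be left to an analysis plan, so their absence is not part of this point.

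What remains is the conflict over whether the arms are districts or clusters, and the missing identifier on district-level costs.

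**Conclusion.** The point holds in a limited form. The protocol contradicts itself on the unit that defines the arms. Study Two randomises clusters selected from districts, while Study Three, 2.1 and 2.4, and Study Two's Non-intervention sites speak of districts. If districts were really the arms, the cluster randomisation and the design effect would not describe the trial, so the wording needs reconciling on either reading.

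With clusters as the unit, district supervision, staff, budget, fuel and remaining finance-report costs cannot be separated by arm wherever a district contains both arms. The arm difference in that component is blurred.

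The size of the distortion is unknown. It depends on the number of study districts, the spread of clusters among them, the share of total cost that arises at district level, and the apportionment used. None of these is stated. Mixed districts are probable under even spread and random allocation, but this is an inference and not something the protocol reports. Costs from the patient, treatment-supervisor and community-health-worker forms, and laboratory and TB clinic time used as unit costs, are not affected. Study II's treatment outcome is not affected either.

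**What to change.** 1. In Study Two (Non-intervention sites) and Study Three, 2.1, describe the arms as intervention and non-intervention clusters. In Study Three, 2.4, define n as the sample size per group.
2. On the District form, replace the aggregate supervision items with one line per supervisory visit: date, cluster or kebele served (or arm, with a code for kebeles outside the study), hours, kilometres and fuel. Where one trip serves both arms, list every cluster visited.
3. Charge these costs to the arm they served. Treat only what is truly joint, such as the general programme budget, as overhead to be apportioned. The apportionment key may be set in the analysis plan.

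The cost is wording in three places and a few fields on one existing form. The downside is slightly more recording per supervisory visit. The fields need to be in place before cost collection starts, because the link from visit to cluster cannot be rebuilt from district totals afterwards.
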